**Fig. 1 Fig1:**
[figure not shown]
Schedule of enrollment, interventions, and assessments

### Study interventions

All study intervention components are delivered centrally by one of the coordinating centers and delivered over a 9-month period. Participants who have not started endocrine therapy medication at the time of registration must initiate the drug within 6 weeks after randomization and begin their allocated intervention within 8 weeks after randomization. Allocated intervention may be stopped prior to completion at the patient’s request or disease progression. The study schema can be found in Fig. 2.

**Fig. 2 Fig2:**
[figure not shown]
Study schema depicting timing of intervention activities and outcome assessment

#### Text message reminder (TMR) component (arms 1 and 3)

Participants receive two types of messages to address adherence behavior: (1) daily text message reminders to take their endocrine therapy medication and (2) monthly interactive adherence check-ins, which help to provide accountability and resolve specific barriers through the provision of pre-set motivational responses. Daily text reminders are delivered from a library of 62 distinct messages designed to encourage medication adherence in a positive manner; text reminders focus on three behaviors: initiation, continuation, and adherence to the prescribed dose, as appropriate. Monthly adherence check-ins ask participants “Over the past 7 days, on how many days did you take your ET [endocrine therapy medication]?” Participants respond with a number 0–7, and any response of 6 or greater triggers a positive message that encourages patients to keep taking the medication. Responses of less than 6 are followed by questions about reasons for missed doses and tips for improving adherence. Participants who report at least 2 consecutive months of adherence problems in response to the monthly adherence check-ins will receive additional texts regarding contact with their physicians/health care team and refer participants back to the text message intervention informational handout provided at the beginning of the study participation. All of the daily text message reminders and interactive responses are based on PACE principles (Presenting detailed information, Asking questions, Checking your understanding, and Expressing concerns), with the most common response being to talk directly with their health care team [36, 37].

#### Motivational interviewing (MI) counseling component (arms 2 and 3)

Participants receive 5 telephone-based behavioral counseling sessions utilizing motivational interviewing to target ET initiation, adherence, and persistence. Counseling sessions last anywhere from 30 to 90 min, are conducted by a trained MI counselor in a one-on-one format, and are tailored to individual participant needs, circumstances, and/or values. Each session follows a standardized, semi-structured guide to help develop motivation and skills to aid adherence. Later sessions utilize a toolbox approach, allowing participants to choose from a list of available activities and topics. This format provides flexibility in how the intervention is delivered to meet individual needs and tailors the intervention to meet the needs of specific ethnic, socio-economic, and other specific problems. A counseling workbook is used to facilitate conversation and support participant adherence between sessions. Counselors, located centrally at a coordinating center, attend 3 days of MI-focused training that includes a combination of didactic sessions, video demonstrations, and practice sessions with role-play to develop and enhance skills. The training also provides detailed information about endocrine therapy, cultural sensitivity and competency, barriers women taking endocrine therapy often face, and potential practical solutions to these barriers.

#### Enhanced usual care component (arms 1–4)

In addition to routine breast cancer care received by each participant by their local oncology care team (“usual care”), participants in all arms receive general health education information for breast cancer survivors, delivered via the CHART tool’s interactive modules on the study website. The CHART behavioral assessment tool aims to strengthen behavioral interventions and collect health behavior data by assessing, improving, and modifying participants’ behavioral risk factors. Modules provided to study participants include physical activity, eating habits, weight, emotional health, tobacco use, alcohol use, sleep habits, and balance.

### Study measures

Baseline sociodemographic data are collected on all participants using the Alliance for Clinical Trials in Oncology patient questionnaire. Key components include self-identified race, gender, ethnicity and language preferences, information on income, household size, insurance, employment status, and selected personal and family health history (Table 1).

**Table 1 Tab1:** Participant study measures

Domains and Measures	# items	Baseline	Months 3, 6, 18	Month 12	Month 24
**Socio-demographics:**					
**Alliance Patient Questionnaire (select items):** Age, gender, ethnicity, race, language, education, marital status, health insurance, household size, income, employment status	13 (9 items at Months 12, 24)	X		X • Marital status • Health insurance • Household size/income • Employment	X • Marital status • Health insurance • Household size/income • Employment
**Medical and Family History**:					
Medical and Family History	7	X		X	X
**Quality of Life/ Psychosocial:**					
PROMIS Global Health Questionnaire	10	X		X	X
Breast Cancer Prevention Trial (BCPT) Symptom Questionnaire	25	X		X	X
PROMIS Depression Short Form 8a	8	X		X	X
Concerns About Cancer Recurrence (CARS); overall concerns subscale only	4	X		X	X
Perceived Stress Scale	10	X		X	
Modified Medical Outcomes Study Social Support (mMOS-SS) Questionnaire	8	X		X	
**ET Medication Use:**					
Medication Understanding and Use Self-Efficacy Scale (MUSE)	8	X	X	X	X
Self-reported ET adherence and persistence	17	X	X	X	X
**Intervention Acceptability**:					
Intervention Evaluation: Acceptability, Appropriateness, Ease of Use	15			X	
Was It Worth It (WIWI) Questionnaire for Alliance clinical trial participation	5			X	
**TOTAL ITEMS:**	130	110	25	126	88
**TOTAL ESTIMATED TIME:**		37	10	42	30

At baseline and key follow-up timepoints, electronically collected patient-reported outcome (ePRO) data are collected using the following validated instruments: PROMIS global health and depression questionnaires for health-related quality of life [38], Breast Cancer Prevention Trial (BCPT) survey for breast cancer-related physical symptoms [39], Concerns About Recurrence scale for cancer worry [40], Perceived Stress Scale [41, 42], Modified Medical Outcomes Study Social Support Survey (MMOS-SS) [43], and Medication Use Self Efficacy (MUSE) scale [44]. Self-reported ET adherence behaviors are also collected using the Self-Reported Endocrine Therapy Adherence and Persistence (SETAP) instrument used by Drs [name] and [name] in multiple prior published studies. The majority of ePRO measures are collected at baseline and 12 and 24 months; the MUSE scale and SETAP are also collected at 3 and 6 months. All patient-reported data are obtained via the Alliance ePRO app which is downloaded to patient’s phones at enrollment and stored along with sociodemographic data and coordinator-entered baseline data in the Medidata RAVE system. This ePRO data collection enables the remote nature of the study, with only the baseline visit being a required face-to-face interaction between site staff and the participant. Participants receive incentive gift cards after completion of surveys at each timepoint.

Data for the primary endpoint of endocrine therapy adherence are collected automatically from participants using an electronic medication event monitoring system (Pillsy Inc, Seattle, WA). An electronic cap is mailed from the coordinating center and distributed to each participant at the baseline visit. Daily adherence data are collected beginning from the first day following electronic pill cap activation on which the cap records an electronic “open” event for 24 months. Adherence is assessed at 12 months as a percentage of days covered, defined as the number of days with at least one “open” event divided by the total number of days in the observation period. Electronic adherence data are returned to Pillsy continuously via Bluetooth connection to the patient’s phone; data for all participants are returned to the study team on a monthly basis via secure data feed and stored in Medidata RAVE. Since the pill cap stores data continuously, periodic disconnections of the cap from its Bluetooth connection do not threaten data integrity if the cap is eventually re-connected. Participants are reminded at four pre-set timepoints of participation to place their cap near their phone and verify connectivity. With the exception of these reminders, data collection is completely passive on the participant’s part and the cap does not issue sounds or other reminders to prompt medication taking.

The amount of missing data in Alliance clinical trials has been minimized, typically to less than 5%, due to a long history of targeted approaches. If the proportion of missing patient information is larger than 5%, we will examine the missingness mechanism by modeling indicators of missing values as a function of baseline patient characteristics, observed outcomes, and missingness of outcomes. Based on this diagnostic exercise, we will determine whether we can enhance the analyses by incorporating certain covariates or whether we need to explore more advanced methods.

### Sample size

Enhanced usual care adherence at 12 months is assumed to be 69%, based on our preliminary studies of pharmacy refill data from claims in Medicare, Medicaid, and private insurance populations, using weighted estimates of 12-month adherence among Black women < 50 years old, non-Black women < 50 years old, Black women ≥ 50 years old, and non-Black women ≥ 50 years old. We hypothesize 81% adherence for the TMR-only and MI-only intervention arms based on preliminary data from the GETSET MI counseling pilot intervention [37, 45]. To maintain a primary family-wise two-sided type I error rate of* α* = 0.05, the two chi-square tests will be conducted with nominal *α* = 0.025. At a 2.5% two-sided significance level, the study will have at least 80% power to detect differences in adherence (81% in single component intervention arms vs 69% in enhanced usual care) if 263 evaluable patients are randomized each to the TMR-only, MI-only, and enhanced usual care arms. Because we anticipate ineligible and loss to follow-up of approximately 11%, consistent with other clinical trials of cancer survivors, we will over-recruit, rendering a recruitment target of 1180 randomized patients total (295 per arm). Power Analysis and Sample Size (PASS) software (PASS v15, NCSS, Kaysville, UT) was used to conduct the power analysis.

Young age and self-reported Black race have been shown to be risk factors for low ET adherence [13, 19, 20]. As such, the study is designed to accrue 30% (or 354 of 1180) of patients who self-identify as Black as well as 30% who are < 50 years old at time of recruitment. Additionally, the ideal case is for race and age to be uncorrelated with one another so that they have independent effects on the outcome of interest. To achieve this, we have defined distinct accrual targets for four non-overlapping groups (i.e., Black women < 50 years old, non-Black women < 50 years old, Black women ≥ 50 years old, and non-Black women ≥ 50 years old) and close accrual for each group independently. The target accrual numbers for each group are shown in Table 2.

**Table 2 Tab2:** Accrual targets by race and age strata

Age (years)	Black	Non-Black	Total
< 50	106	248	354
≥ 50	248	578	826
Total	354	826	1180

### Randomization and strategic staged closure

Patients are randomized using a dynamic allocation system based on the method by Pocock and Simon [46] that continuously balances the allocation of participants across the four treatment groups and race (black vs. non-Black) and age (≥ 50 vs. < 50) stratification factors, regardless of which race and age strata remain open at the time of randomization. To avoid the algorithm being deterministic, a level of randomness is added to the algorithm such that patients are assigned to the arm that leads to more imbalance 10% of the time. Participants are consented and enrolled to the trial by local site coordinators via the Oncology Patient Enrollment Network (OPEN), a web-based registration system integrated with the regulatory and roster data as well as the lead protocol organization (LPO) registration/randomization system and the Theradex Interactive Web Response System (IWRS) which is used for retrieval of the patient registration/randomization assignment. Using these systems, participant assignment to study arms is automatically completed upon enrollment. Neither participant nor study staff are blinded to intervention allocation since this would not be feasible in a behavioral intervention. However, the primary outcome assessment is measured objectively using a medication event monitoring cap, and investigators are effectively blinded to primary endpoint data since data are collected and centrally managed externally by Alliance’s RAVE system and analysts. To achieve target numbers of patients in each race and age stratum as laid out in the statistical plan, while still accruing the overall study as quickly as possible, we use a process we describe as “strategic staged closure”. Strategic staged closure is the process of monitoring accruals according to the study’s pre-specified sub-group strata (in this case, younger Black, older Black, younger non-Black and older non-Black) and closing each stratum individually as it approaches its target accrual. The study chairs meet monthly throughout the study with the statistical team to review the pace and cumulative numbers of patients accrued in each stratum. As numbers approach the desired target for each stratum, a memorandum of impending closure is prepared for distribution to participating sites setting a date for closure estimated from the recent pace of accruals in that sub-group. We aim to notify sites of impending closure approximately 2 weeks in advance to allow any patients in active screening to consent to the study before stratum closure.

## Outcomes

### Primary endpoint

The primary endpoint is ET adherence at 12 months post-randomization as measured by electronic pill monitoring cap (Pillsy-reported). Patients will be labeled as adherent if the proportion of days covered by any ET medication is at or above 80% (i.e., taking ET at least 292 of 365 days). Women who do not take ET for at least 292 days will be deemed non-adherent at 12 months. The primary analysis will be based on a modified intention-to-treat population (mITT), defined as all women who signed a consent form, met the eligibility criteria, were randomized, and took ET on at least one occasion; furthermore, these women will be analyzed in the arms to which they were randomized. For the primary analysis, two comparisons will be made using two chi-squared tests: TMR-only versus enhanced usual care and MI-only versus enhanced usual care. For each comparison, statistical significance will be assessed at the 2.5% level. Should either TMR-only or MI-only arms achieve statistical significance at its allocated α-level (or accumulated unused α-levels if both achieve statistical significance), then the TMR + MI vs enhanced usual care comparison will be assessed and the unused α-level passed down and applied to determine statistical significance. In this way, the type I error rate applied to the primary family of endpoints can be controlled at the 5% level.

As a sensitivity analysis, we will assess if the intervention effects on ET adherence differ by the stratification factors of age and race. Therefore, logistic regression is planned to model the binary measure of adherence at 12 months separately for each intervention vs enhanced usual care comparison so that three separate logistic regression models will be estimated. Covariates included in each logistic regression model will be age (< 50 years; ≥ 50 year), race (Black women; non-Black women), intervention arm assignment, and the interaction terms between each stratification factor (age and race) and intervention arm assignment to ascertain whether the magnitude of the intervention effect is different across the levels of age and race. Statistical significance of the interaction terms will be assessed at the 10% level with the likelihood ratio test comparing models with and without the interaction terms.

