## Discussion

The Alliance A191901 GETSET trial is innovative because we will evaluate not only the efficacy of the proposed interventions, but also patient-reported outcomes and economic outcomes associated with the interventions within the same research proposal. In addition, we employ stratified sampling to achieve a diverse sample, oversampling both Black women and younger women to ensure adequate representation. This strategy will also inform the design of future clinical trials and efforts to increase enrollment of participants from underrepresented populations. We also use novel approaches to behavioral intervention that can be delivered remotely at scale with low burden to patients and research coordinators, thus appealing to a wider array of patients and research sites than traditional clinical trials. GETSET also represents one of the largest, completely remote behavioral interventions administered within the Alliance cooperative research group, and our hope is to show the feasibility of executing this type of intervention on a large scale.

A temporary suspension of accrual to the trial at all sites began in November 2022, approximately 21 months into recruitment. This temporary suspension was for administrative reasons, and not associated with rate of recruitment, IRB requirements, or adverse events experienced by participants. The vendor supplying the electronic medication event monitoring caps experienced unanticipated problems activating the equipment, and therefore, accrual was temporarily suspended to new patient registration until this issue is resolved. During the suspension, patients previously accrued to the study have continued to follow protocol-specified treatment and testing schedules, as planned, and data collection has continued as per protocol. We anticipate completion of the original target accrual after re-opening, expected in October 2024.

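### Sample size, primary endpoint and missing-data text disagree on how women without full 12-month cap data are handled, leaving the stated power conditional and the comparison open to bias

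*Protocol article*

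**What the plan says.** Three parts of the protocol article bear on a woman whose cap record is incomplete at 12 months.

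- **Outcomes, Primary endpoint.** The endpoint is cap-measured. The threshold is 80% of days covered, spelled out as 292 of 365 days, and "Women who do not take ET for at least 292 days will be deemed non-adherent at 12 months". The mITT set is every consented, eligible, randomized woman who took endocrine therapy (ET) at least once. It has no requirement for 12-month cap data.
- **Methods, Sample size.** "At a 2.5% two-sided significance level, the study will have at least 80% power to detect differences in adherence" of 81% versus 69% "if 263 evaluable patients are randomized each to the TMR-only, MI-only, and enhanced usual care arms". The step to 295 randomized per arm is justified this way: "Because we anticipate ineligible and loss to follow-up of approximately 11%, consistent with other clinical trials of cancer survivors". The 11% is not split between the two causes.
- **Methods, Study measures.** Adherence is the number of days with an open event divided by the days in the observation period. Stored data make temporary gaps recoverable: "periodic disconnections of the cap from its Bluetooth connection do not threaten data integrity if the cap is eventually re-connected". On missing data: "If the proportion of missing patient information is larger than 5%, we will examine the missingness mechanism", using a model that includes observed outcomes. The analysis is then to be adapted in the light of that exercise.

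**The concern.** The sections describe different sets of women and different denominators. A woman lost for good before day 292 is counted out in the sample size. She stays in the mITT denominator, where she cannot reach 292 recorded days. Under Study measures she may be scored on a shorter period if that period ends at loss. For example, a cap lost at day 30 with 25 open days gives 25/30 = 83%, which passes the 80% threshold but fails the 292-day rule.

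Two things are at stake. First, if lost women are scored as failures, both rates and their difference may shrink, and power may fall below the stated level. Second, allocation is open and the cap sends its data through the participant's phone, so permanent data loss could differ by arm. A rule that scores absent data as non-adherence would turn such a difference into an apparent treatment effect. The missing-data text does not settle this: it names no default method, acts only above 5% although the trial's own attrition allowance is about 11%, and leaves the choice until outcomes have been examined.

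**Working it through.** **Inputs.** From Sample size: adherence 69% and 81%, two-sided alpha 0.025 per comparison (z = 2.2414), 263 evaluable and 295 randomized per arm, about 11% ineligible or lost. From Primary endpoint: the 292-day rule and the mITT definition. The split of the 11% and all arm-specific loss rates below are assumptions.

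**Formula.** With p̄ = (p1 + p2)/2, s0 = √[2p̄(1−p̄)/n] and s1 = √[(p1(1−p1) + p2(1−p2))/n], power = Φ[(|p2−p1| − z·s0)/s1]. The continuity-corrected version subtracts 1/n from |p2−p1|.

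**Step 1: the plan's own figure.** For n = 263, 0.69 versus 0.81: p̄ = 0.75, s0 = 0.03776, s1 = 0.03740. Power is 82.8%, or 80.1% corrected. The corrected formula returns exactly 263 per arm for 80% power (247 without correction). 1 − 263/295 = 10.8%, which matches about 11%. The stated figure reproduces on its own inputs.

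**Step 2: literal 292-day rule, rates describing women not lost.** Let i be the ineligible fraction, which the mITT removes, and 0.11 − i the lost fraction, which it keeps. Then n = 295(1 − i), the lost share of the mITT is L = (0.11 − i)/(1 − i), and both rates are multiplied by 1 − L. This assumes no lost woman reached 292 recorded days.

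| Ineligible / lost | n per arm | Rates | Power | Corrected |
|---|---|---|---|---|
| 0% / 11% | 295.0 | 61.4% vs 72.1% | 69.7% | 66.5% |
| 3% / 8% | 286.1 | 63.3% vs 74.3% | 72.8% | 69.7% |
| 6% / 5% | 277.3 | 65.3% vs 76.7% | 76.2% | 73.2% |
| 8% / 3% | 271.4 | 66.7% vs 78.4% | 78.7% | 75.8% |
| 9% / 2% | 268.4 | 67.5% vs 79.2% | 80.0% | 77.1% |

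First row in full: p̄ = 0.6675, s0 = 0.03879, s1 = 0.03854, (0.1068 − 2.2414 × 0.03879)/0.03854 = 0.515, Φ = 69.7%.

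If total attrition were below 11%, the shortfall would be smaller. With all 295 eligible, 3% loss gives 82.7% (80.2% corrected) and 5% loss gives 79.5% (76.8%).

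**Step 3: same rule, rates already counting lost women as non-adherent.** The rates stay at 69% and 81%, and only ineligible women leave.

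- 0% ineligible, n = 295: 87.2% (85.1% corrected).
- 8% ineligible, n = 271.4: 84.0% (81.5% corrected).

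So the direction of the power result turns on what 69% and 81% represent. The 69% comes from pharmacy refill claims, and the article does not say how those counted drop-out.

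**Step 4: unequal loss, illustration only.** Both arms truly at 69%, n = 295, loss of 14% versus 8%: 0.69 × 0.86 = 59.3% and 0.69 × 0.92 = 63.5%. The spurious difference is 4.1 points and the two-sided rejection probability is 11% instead of 2.5%. Reversing the arms reverses the sign. Equal loss of 11% in both arms keeps 2.5%. The bias can also hide a real effect: with true rates of 69% and 81%, loss of 6% in usual care and 11% in the intervention arm leaves 7.2 points and 36% power.

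**The case against.** The strongest reply is that no sentence scores absent cap data as non-adherence. The sentence on 292 days speaks of not taking ET, and a separate missing-data paragraph would have little to act on for the primary endpoint if missing simply meant non-adherent. The article also refers to a full protocol and a statistical plan that are not shown, where day-level scoring and imputation models normally sit. This stands as far as it goes: the article is ambiguous, and the detail of an imputation model is not missing from it. It does not remove the conflict, because the article itself gives two denominators and an evaluable set that differs from its analysis set.

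A reader might infer that the trial will not have 80% power. The documents do not support that. The shortfall needs the literal reading, an undocumented split of the 11%, and rates that exclude lost women; Step 3 shows power at or above 80% under the opposite assumption. The article also says missing data in this group's trials are typically below 5%.

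A reader might also infer a false effect favouring text messaging, since those women are messaged daily. No arm-specific loss is reported. All arms use a smartphone, supplied if needed, and the same cap app. Transfer is passive, the four connectivity reminders are not described as differing by arm, and stored data are recoverable on reconnection. Only permanent loss matters, and its direction is unknown.

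Nor is the Discussion's report that "The vendor supplying the electronic medication event monitoring caps experienced unanticipated problems activating the equipment" evidence of lost outcomes. It concerned activation and new registrations, and the same paragraph says data collection from enrolled women continued.

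**Conclusion.** The inconsistency between Study measures, Sample size and Primary endpoint is real and touches the primary analysis. Its numerical consequence is conditional. On the literal 292-day reading, with 69% and 81% applying to women not lost and no lost woman reaching 292 recorded days, power at 295 randomized per arm is about 70% to 79% for 11% down to 3% lost (67% to 76% corrected). If the rates already include lost women as failures, there is no shortfall. Bias from unequal permanent data loss is possible in either direction, but its size is unknown; the figures in Step 4 show sensitivity and are not a forecast. The point deserves correction before the data are analysed by arm. It is not a demonstrated failure of the design, and it ranks below a must-fix held with high confidence.

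**What to change.** 1. Use one denominator in Study measures and Primary endpoint.
2. Distinguish a working cap that was not opened (a non-adherent day) from permanently absent cap data, and keep confirmed ET discontinuation as non-adherent.
3. Replace the 5% trigger and the data-driven choice with one primary method fixed before any unblinded analysis. One option is multiple imputation by arm using age, race, earlier cap data and self-reported adherence. Silence after the last transmission may itself reflect stopping, and lost women may also lack self-reports, so add two sensitivity analyses: all missing counted as non-adherent, and a tipping-point analysis.
4. Align the evaluable set in Sample size with the mITT set, and state the assumed split of the 11%.
5. If counting missing as non-adherent stays primary, say whether 69% and 81% include lost women. If they do not, restate power as about 70% to 79% (uncorrected).

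The cost is wording and modest programming, and possibly a less favourable stated power. No new patients or data are needed.

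### The primary chi-square tests ignore age and race, the trial's own balancing factors, and are therefore mildly conservative: a minor loss of efficiency that costs almost nothing to recover

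*Protocol article*

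**What the plan says.** **Allocation.** Under Randomization and strategic staged closure, the article describes a Pocock-Simon dynamic system that "continuously balances the allocation of participants across the four treatment groups and race (black vs. non-Black) and age". A 10% random element is added.

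**Prognostic status.** The Sample size section says: "Young age and self-reported Black race have been shown to be risk factors for low ET adherence". The trial enriches for both groups (30% each) and sets accrual targets for the four age-by-race cells in Table 2. The usual-care rate is itself a weighted average over those same four cells.

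**Primary test.** Under Primary endpoint: "For the primary analysis, two comparisons will be made using two chi-squared tests: TMR-only versus enhanced usual care and MI-only versus enhanced usual care". Each test is at the 2.5% level, and the combination arm is tested against usual care only if at least one of them succeeds. No stratification or covariate is named.

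**Where age and race are used.** They enter only three logistic models labelled a sensitivity analysis. The stated purpose is to test arm-by-age and arm-by-race interactions at the 10% level by likelihood ratio.

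**The concern.** When allocation is forced to be even on factors that predict the outcome, the difference in proportions between arms varies less from trial to trial than under simple randomisation. The ordinary chi-square does not know this. It takes its variance from the overall pooled proportion, which still includes the spread between strata, so its standard error is somewhat too large. The p-values are then somewhat too large, the actual type I error falls below nominal, and some power is lost relative to a test that conditions on the strata.

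The article names the primary test and separately describes the models that do use age and race, so this is a stated choice and not a detail left for the analysis plan. At stake is a little power in each first-step comparison and, through the gate, a slightly lower chance of reaching the combination comparison.

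**Working it through.** **Inputs from the article.** Usual care: "Enhanced usual care adherence at 12 months is assumed to be 69" (per cent). Interventions: "We hypothesize 81% adherence for the TMR-only and MI-only intervention arms". Size: "if 263 evaluable patients are randomized each to the TMR-only, MI-only, and enhanced usual care arms". Level: "At a 2.5% two-sided significance level, the study will have at least 80% power to detect differences in adherence". Attrition: "we anticipate ineligible and loss to follow-up of approximately 11" (per cent). Cell shares from Table 2, each divided by 1180: 106 (9.0%) Black under 50, 248 (21.0%) non-Black under 50, 248 (21.0%) Black 50 or over, 578 (49.0%) non-Black 50 or over.

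**Assumption.** The article gives no stratum rates. I assume a logit model with the same odds ratio (OR) for adherence for Black race and for age under 50, and solve the intercepts so that the cells average to 69% and 81%.

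**Step 1: reproduce the plan's figure.** With z = 2.2414 for two-sided 0.025, 0.8416 for 80% power, and a mean proportion of 0.75:

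- n = [2.2414·√(2·0.75·0.25) + 0.8416·√(0.69·0.31 + 0.81·0.19)]² / 0.12² = 246.2, so 247 per arm.
- With continuity correction: (246.2/4)·[1 + √(1 + 4/(246.2·0.12))]² = 262.6, so 263. This matches the article.
- 263/(1 − 0.11) = 295.5 against the stated 295, and 4 × 295 = 1180.
- At 263 per arm the uncorrected chi-square has power Φ[(0.12 − 2.2414·0.03776)/0.03740] = Φ(0.946) = 82.8%. With the correction it is 80.1%.

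The comparisons below use uncorrected tests throughout.

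**Step 2: actual level of the unadjusted test.** Let w be the cell shares and p the cell rates at a common overall rate of 75%. The test assumes variance 0.75·0.25 = 0.1875 per observation; with strata balanced the true value is Σw·p(1−p). With r the ratio of true to assumed, actual level = 2[1 − Φ(2.2414/√r)]. At OR 0.50: r = 0.1799/0.1875 = 0.960, and 2[1 − Φ(2.288)] = 0.0221.

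**Step 3: power at 263 per arm.** Let W = Σw[p_c(1−p_c) + p_t(1−p_t)], where p_c and p_t are the control and intervention cell rates, and let p̄ be their mean in each cell.

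- Unadjusted: Φ{[0.12 − 2.2414·√(2·0.1875/263)] / √(W/263)}
- Stratified: the same with 0.1875 replaced by Σw·p̄(1−p̄)

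At OR 0.50: W = 0.3530 and Σw·p̄(1−p̄) = 0.1803. Unadjusted: (0.12 − 0.08464)/0.03664 = 0.965, giving 83.3%. Stratified: (0.12 − 0.08298)/0.03664 = 1.010, giving 84.4%.

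The last column is the increase over 263 that the unadjusted test would need to match the stratified power.

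| Assumed OR per factor | Control adherence, younger Black / older non-Black | Actual level | Power, unadjusted | Power, stratified | Equivalent extra patients |
|---|---|---|---|---|---|
| 1.00 | 69% / 69% | 0.0250 | 82.8% | 82.8% | 0% |
| 0.80 | 62% / 72% | 0.0247 | 82.8% | 82.9% | 0.3% |
| 0.61 | 53% / 75% | 0.0235 | 83.0% | 83.6% | 1.4% |
| 0.50 | 47% / 78% | 0.0221 | 83.3% | 84.4% | 2.8% (270.3/263) |
| 0.37 | 37% / 81% | 0.0194 | 83.8% | 86.0% | 5.7% (277.9/263) |

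**Step 4: check without assuming perfect balance.** Four-arm minimisation on the two margins with a 10% random element was simulated, with 200,000 replicates per scenario and the null set at 69% in both arms.

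- OR 0.50: level 0.0222 unadjusted against 0.0249 for Cochran-Mantel-Haenszel (CMH); power 83.4% against 84.4%.
- OR 0.33: level 0.0188 against 0.0249; power 83.9% against 86.7%.

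For the same null the closed form gives unadjusted levels of 0.0219 and 0.0178, so real minimisation is slightly less conservative than perfect balance. CMH held its level.

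**The case against.** The strongest reply is that nothing in the plan is wrong. The Sample size and Primary endpoint sections agree, 263 per arm reproduces for the planned test, at least 80% power is kept in every scenario above, and type I error is never above nominal. All of that stands, and it limits the point to efficiency.

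Three further objections:

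- **The odds ratios are not in the article.** True. Calling age and race risk factors fixes the direction but not the size. With weak factors (0.80) the gain nearly vanishes, and nothing in the article supports a spread as wide as 37% against 81%.
- **Balancing is not wasted.** A reader might infer that the trial pays for minimisation and then gets nothing from it. The figures contradict this: power of the planned chi-square rises from 82.8% to 83.8% as the factors become more prognostic. The stratified test only gains more.
- **An adjusted model will be fitted anyway.** The likelihood ratio test needs a model without interactions, which contains arm, age and race. This stands only in part. That model serves as the comparator for an interaction test and is not presented as an adjusted test or estimate of the intervention effect.

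**Conclusion.** The point holds as a minor matter of efficiency. The planned chi-square tests are valid, mildly conservative, and slightly less powerful than a test stratified on the two balancing factors. The gain is about one percentage point of power or less unless the odds ratio for each factor is more extreme than about 0.50. It reaches about two points (about 6% more patients) only at 0.37.

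A reader might infer that error control is compromised, that the trial is underpowered, or that a substantial share of the sample is wasted. The documents support none of these: the level errs downward, the promised power is met, and the larger savings need stratum differences that the article does not report.

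The direction rests on age and race being prognostic, as the article states. The size rests on the assumed common odds ratio, no interaction with arm on the logit scale, and Table 2 shares among evaluable patients.

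**What to change.** Before any comparison of primary-endpoint data by arm, prespecify the following:

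- A Cochran-Mantel-Haenszel test over the four age-by-race cells for TMR-only and for MI-only against enhanced usual care, and for the gated TMR + MI comparison. Each keeps the alpha and gating already planned.
- The stratum-adjusted risk difference with its confidence interval as the reported effect. This stays on the difference-in-proportions scale used for sizing; a logistic model would move the target to a conditional odds ratio.
- The unadjusted chi-square as a supportive analysis, and the interaction models as they are.

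The smallest cell would hold about 24 evaluable patients per arm (263 × 0.090), so four strata are workable. The cost is a change of wording and of one procedure. It needs no new data or patients and no change to the sample size, and the simulation shows the nominal level is kept. The article reports accrual still incomplete (1024 of 1180) and no results, so the change could still be made in advance.
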